**Fig. 1 Fig1:**
[figure not shown]
The evaluation of FLASH – study flowchart

### Outcome measures

#### Primary outcome

The primary outcome will be change in glycaemic control analysed by estimating HbA_1c_.Testing will be performed in a central laboratory using the high-performance liquid chromatography (HPLC) method (normal range, 4.3–6.1% or 23.5–43.2 mmol/mol). Laboratory personnel will be blinded to the treatment allocation. All blood samples will be analysed once and then destroyed; specimens will not be stored for future use.

#### Secondary outcomes

Secondary outcomes will include medical and psychosocial measurements. These secondary outcomes will include: (1) time spent in different glycaemic ranges (hypo-/normo-/hyper-glycaemic status: < 70 mg/dL/70–180 mg/dL/> 180 mg/dL); variability of glucose level; (2) episodes of severe hypoglycaemia; (3) quality of life; (4) diabetes distress; (5) depression; (6) empowerment; and (7) satisfaction with the device and with the education.

### Assessments

Patients will be assessed at *three time points* (Fig. 1):At baseline (t0)At the end of FLASH, after the fourth session (t1)At follow-up 6 months after the end of FLASH (t2)

The first assessment will take place, as described above, over two visits with an interval of 2 weeks. The second assessment will occur immediately at the end of the FLASH programme or within 2 weeks after its end. At this visit the patients’ glycaemic status and satisfaction with the device will be assessed. Additionally, in the intervention group, satisfaction with the FLASH programme will also be evaluated. The third and last assessment will be at follow-up 6 months after the end of the FLASH programme. At this visit patients will answer follow-up questionnaires, give blood samples, and return the flash glucose monitoring device to the study personnel.

All assessments will be made by the personnel at the respective centre. All study centres are instructed by a personal visit and each study centre was offered a hotline and was audited by telephone. In addition, 50% of the study centres will be audited by FIDAM to check the quality of study conduct. Glycaemic data from the flash glucose monitoring system will be uploaded via Diasend®; thus, FIDAM can identify online incomplete data and notify the study centres whenever necessary.

Glucose values recorded through the flash glucose monitoring reader will be uploaded through the web-based diabetes management system Diasend®, which will be installed on computers at each study centre. With individual patient codes, all flash glucose monitoring data will be uploaded by the responsible personnel at each study centre during the visits. Demographic data (age, gender, nationality, family status, housing situation, and educational level) and additional clinical data (weight and height, comorbidities, and details of the diabetes therapy) will be entered into Case Report Forms (CRFs) by the concerned physician. All CRFs will be in paper-and-pencil form; no electronic Case Report Forms (eCRFs) will be used. FIDAM will be responsible for the management of all collected data. This study is registered at ClinicalTrials.gov (identifier: NCT03175315) where all relevant information is available to the public. There will be no external safety committee since this is a non-pharmacological intervention. The incidence of serious adverse events and device-related adverse events will be collected via standardised reporting forms and reported to FIDAM.

Data on participants’ emotional state and their experiences in living with diabetes will be collected through diabetes-, programme-, and device-related questionnaires:Diabetes Acceptance Scale (DAS) – to assess illness acceptance. Patients mark their intensity of agreement with 28 statements on a 4-point scale from 0 (not true) to 3 (totally true). A higher score indicates a higher level of acceptance [6]Diabetes Distress Scale (DDS) – a validated self-report scale to assess the current level of diabetes-related emotional distress. It has 28 items rated on a 6-point scale from 0 (no problem at all) to 5 (a very serious problem) [7]Problem Areas in Diabetes (PAID) Scale – a self-report form which builds up an index of emotional pressure, using 20 items rated on a 5-point scale from 0 (not a problem) to 4 (serious problem) [8]General quality of life – the widely used World Health Organisation Well-being Index (WHO-5) self-report form to assess general quality of life. The scale consists of five questions, rated on a 6-point scale from 0 (at no time) to 5 (all the time). It is a measure of sense of well-being over the last 2 weeks [9]Health-oriented Quality of Life (EQ-5D; German version) – to assess the actual health status and to grade problems in five fields [10]Centre for Epidemiologic Studies Depression Scale (CES-D; German version) – to assess depression; it uses nine items rated on a 4-point scale from 0 (never/rarely) to 3 (often/always) [11]Personal Health Questionnaire (PHQ-8) – to assess mood issues over the last 2 weeks; eight items are rated on a scale that ranges from 0 (never) to 3 (nearly every day) [12]Hypoglycaemia Fear Survey (HFS) – to assess worries and behaviour related to hypoglycaemic events; it uses 18 statements related to troubles with hypoglycaemia at a variety of events; patients rate the troubles experienced on a 5-point scale that ranges from 0 (never) to 4 (always) [13]Diabetes Empowerment Scale – to assess empowerment and psychosocial self-efficacy; it uses 21 items to examine how difficulties in the daily routine are handled [14]Hypoglycaemia Awareness Scale (German version) – this consists of nine items. Scores range from 0 (maximum hypoglycaemic awareness) to 9 (minimum hypoglycaemic awareness) [15]Satisfaction with diabetes therapy – patients answer 10 questions on how satisfied they were with several aspects of their diabetes therapy over the last 4 weeks, with higher score indicating a higher level of dissatisfaction [16]Satisfaction with FLASH – the intervention group will be asked to evaluate FLASH. Participants will answer a total of 16 itemsFidelity measure – in addition as a fidelity measure an 11-item scale will be applied. Participants of FLASH will be asked to what degree the educators addressed individual goals, how supported they felt in adjusting their diabetes therapy, and if the programme was presented in a structured wayGlucose Monitoring Satisfaction Survey (GMSS) – patients will be asked to indicate their thoughts and emotions while using the flash glucose measurement system; there are 15 items that can be scored on a scale ranging from 1 (does not apply at all) to 5 (applies very strongly) [17]Use of technical possibilities – patients will be asked to describe their use of all the technical possibilities of the flash glucose monitoring system within the last 4 weeks; responses are graded on a scale ranging from 0 (not at all) to 4 (several times a day)Experiences with glucose measurement (Glucose Monitoring Assessment Tool; GMAT) – 19 statements are used to build up a score that reflects experiences related to measurement of glucose level; for example, ‘the measurement of glucose is awkward for me’ or ‘I avoid measuring my glucose level if I have the feeling that the level is high’. [18]

Answering all the questionnaires will take about 30 min for each patient (the booster questionnaire administered at the end of the FLASH programme is slightly smaller). Figure 2 presents a summary of all the measurements.

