## Methods/design

### Study setting

The study is designed as a multicentre study. A total of 40 diabetes outpatient treatment centres located across Germany have been invited to recruit eligible patients for the study. A study centre is defined as a medical practice run by a diabetologist and where diabetes nurses or certificated diabetes educators (CDE) are also available. The course instructors for FLASH will be CDE. Prior to the study, the course instructors will undergo an intensive 8-h training in the study protocol and the education and treatment programme. This programme will be conducted by the research team. Course instructors will be provided with a written curriculum and audiovisual teaching material, along with detailed descriptions of each slide. Additionally, trainers from the coordination research institute (Research Institute of Diabetes Mergentheim: FIDAM) will visit each participating medical centre, and course instructors can then resolve any doubts about the conduct of the programme. In these visits FIDAM employees will confirm that the slides of the FLASH will operate and could be displayed in each medical praxis and that the course instructor knows how to conduct the programme, fully understands the content of the programme, can clarify any likely questions, and knows how to upload the therapy data from the flash glucose monitoring reader to Diasend®. During the course of study, all study centres will have a hotline to FIDAM for support. FIDAM will communicate with all participating study centres via newsletters where every new development can be presented promptly and reliably. Conversely, the coordinating centre will be available for the responsible personnel in the study centres for the entire duration of the study. In addition to conducting the education and treatment programme, the physicians at the study centres will be responsible for the therapy of their patients during and after the study.

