**Fig. 2 Fig2:**
[figure not shown]
Overview of all measurements at the different assessment points

Financial grants will be issued for patients who complete the study. These financial grants will not be given to the patients but to the study centres to compensate them for the additional effort (i.e. recruitment of patients, informing the patients about the study, obtaining informed consent, conduct of treatment, checking questionnaire data and electronic data for completeness, answering queries, and reporting serious or device-related adverse events). All educational materials will be supplied free to the study centres and patients.

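### The FLASH satisfaction and fidelity forms, which rate the practice's own programme and educators, pass through that practice, so both are open to favourable answering of unknown size

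*Protocol article*

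**What the plan says.** Four statements in the protocol article bear on this.

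- **Who assesses** (Assessments): "All assessments will be made by the personnel at the respective centre".
- **Who checks the forms** (Assessments, paragraph after Fig. 2): the tasks for which centres are compensated include "checking questionnaire data and electronic data for completeness, answering queries".
- **Who teaches, and where** (Study setting): on the teachers, "The course instructors for FLASH will be CDE"; and on the sites, "A study centre is defined as a medical practice run by a diabetologist and where diabetes nurses or certificated diabetes educators (CDE) are also available". By the same section, the centre's physicians are responsible for the patients' therapy during and after the study.
- **What is rated** (Assessments): for programme satisfaction, "the intervention group will be asked to evaluate FLASH", with 16 items. A further 11-item scale is described as the fidelity measure: "Participants of FLASH will be asked to what degree the educators addressed individual goals, how supported they felt in adjusting their diabetes therapy".

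Under Secondary outcomes, item 7 includes satisfaction with the education. Fidelity is not in that list. Satisfaction with FLASH is collected at the second assessment, at the end of the programme or within two weeks. The text gives no time point for the fidelity scale, and the measurement overview (Fig. 2) is not shown.

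**The concern.** People asked to judge a service tend to answer more kindly when they believe the provider may see the answers. Here the provider is the practice that taught the course and continues to treat the respondent. These two forms differ from the rest of the questionnaire battery because their subject is the practice's own work.

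Two readings are at stake. One is a named secondary outcome, satisfaction with the education. The other is whatever a reader concludes about delivery. If the fidelity score is generous, poor delivery can go unnoticed, and a null HbA1c result becomes harder to explain. The Discussion foresees certification of the programme in Germany if it proves beneficial, so how well it was received and delivered will interest readers beyond the trial.

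**Working it through.** **1. Does the plan's own figure bear on this?** The only relevant number is the sample size, and it reproduces. With a difference of 0.3, an SD of 0.7, two-sided alpha of 0.05 (the article does not state sidedness) and power of 0.8, n = 2 × (1.960 + 0.842)² × 0.7² / 0.3² = 85.5, so 86 per group. Allowing for 20% non-evaluable, 86 / 0.8 = 107.5, so 108 per group and 216 in total. These figures concern HbA1c and do not help to size a bias in a satisfaction score.

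**2. The route of the forms, statement by statement.**

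| Step | What the article states | What it does not state |
|---|---|---|
| Assessment | Centre personnel make all assessments | Whether the course instructor is one of them for her own patients |
| Checking | Centres check questionnaire data for completeness | That anyone reads answers beyond completeness |
| Return | – | Sealed, anonymous or direct return to FIDAM |
| Teaching | Instructors are certificated educators; centres are practices with nurses or such educators | That each patient's rated educator handles that patient's form |

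Checking a form for completeness requires handling the answered form. The first two rows therefore put the answers within the practice's sight by stated assignment, whatever happens in the other two.

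**3. Would patient codes protect the respondent?** The article plans 216 patients and has invited 40 centres: 216 / 40 = 5.4 patients per centre on average. If the arms are split evenly within centres (an assumption), that is 5.4 / 2 = 2.7 FLASH patients per centre. Course groups have three to eight members. In numbers this small a code conceals little from staff who know the patients.

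**4. Can the data expose the problem?** No. Both scales are given only to FLASH participants, so there is no comparison group in which favourable answering could be seen or cancelled out.

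**5. Is there another source on fidelity?** The article describes eight hours of instructor training, a written curriculum with slide descriptions, a preparatory visit to every centre, telephone audits, and audits of half the centres for quality of study conduct. Training and preparatory visits show that instructors can deliver the programme. No observer rating of sessions is described.

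**6. Can a size be given?** No figure in the documents allows it. Any shift in SD units would be an assumption, and the resulting bias would simply equal the shift assumed.

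**The case against.** **The link to the rated educator is inferred.** This stands. The article does not say that the instructor collects or reads her own patients' forms, and a centre has other staff. Details of form return may sit in the full protocol or a centre manual, so their absence from an article is no fault in itself. What remains is the stated assignment of assessment and checking to the centre.

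**The consequence is limited.** This also stands. The two scales yield no between-arm effect, fidelity is not a listed outcome, and the planned analysis gives it no role. A reader might infer that the fidelity score will be used to interpret the HbA1c result, but no passage says so.

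**A reader might extend the point to well-being, distress, empowerment and device satisfaction.** The documents do not support this. Forms from both arms go through centre staff at the practice that treats the patients. A difference between arms would come mainly from patients knowing their group, which is unavoidable for an education programme and which envelopes would not remove. Supposing a shift of 0.1 to 0.3 SD in the FLASH arm alone does not rescue the argument, because the input is returned as the output. Even its upper end is borderline. With 108 per arm the standard error is sqrt(2/108) = 0.136, and 0.3 / 0.136 = 2.2. With the 86 evaluable per arm that the article plans for, it is sqrt(2/86) = 0.152, and 0.3 / 0.152 = 1.97.

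**The completeness check has value.** This stands and shapes the fix. The online check by FIDAM covers glucose uploads only, so the check at the centre is the only completeness safeguard described for questionnaires. Removing it throughout could add missing data to every questionnaire outcome, to be filled by last observation carried forward.

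**Conclusion.** The point holds in a narrow form. The FLASH satisfaction scale and the patient-rated fidelity scale are at risk of favourable answering, because patients rate their own practice's programme and educators on forms that the practice handles. The size is unknown and cannot be derived from the documents.

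A reader might conclude that these results are biased upwards, or would look good whatever was delivered. The documents support a risk only; they prove neither direction nor magnitude. The primary outcome is measured by a blinded central laboratory and is untouched, as is the sample size. The comparative questionnaires are not shown to be affected by this route.

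The conclusion assumes that no unpublished centre instruction already provides for sealed return. If one does, the point falls away. This is a cheap improvement and not a threat to the trial's main conclusion.

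**What to change.** For the FLASH satisfaction form and the fidelity form only:

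- have patients complete them without the course instructor present;
- have them returned in a sealed, coded envelope to FIDAM, which already manages all collected data;
- tell patients that the practice will not see their answers;
- exempt both forms from the centre's completeness check, with the centre confirming dispatch only.

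Keep the centre's completeness check for all other questionnaires.

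The cost is envelopes, postage and a line in the centre instructions, with no extra visits or staff. The downside is some more missing items on these two forms, since nobody at the centre will prompt for them. If the forms have already been collected through the practices, report both scales descriptively and state how they were collected.

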**Fig. 2 Fig2:**
[figure not shown]
Overview of all measurements at the different assessment points

Financial grants will be issued for patients who complete the study. These financial grants will not be given to the patients but to the study centres to compensate them for the additional effort (i.e. recruitment of patients, informing the patients about the study, obtaining informed consent, conduct of treatment, checking questionnaire data and electronic data for completeness, answering queries, and reporting serious or device-related adverse events). All educational materials will be supplied free to the study centres and patients.

### Planned data analysis

Continuous data over all three time points will be summarised using descriptive statistics. Differences across the time points will be calculated for each group. The distributions of these differences will be compared using analysis of variance (ANOVA) for repeated measurements, with the FLASH group as the independent variable. If significant baseline differences are seen, the respective baseline values will be used as covariates.

Sometimes the questionnaire data may be skewed and may not fulfil the criteria for interval data. Assuming that at least rank-order data are available from the questionnaires, we will use either non-parametric tests for the evaluation of questionnaires and glucose data, or perform a transformation of the scores and glucose parameters into van der Waerden scores before applying parametric tests. Based on the data distribution and the scale of measurement, appropriate statistical methods will be selected. In the case of categorical data determined over several time points, we will use logistic regression analysis with adjustment for baseline values.

Statistical testing will be conducted at a significance level of *α* = 0.05. All analyses will be performed using SYSTAT version 12.0. For the intention-to-treat analysis missing data will be substituted by the last-observation-carried-forward method.

All data will be treated as confidential and be stored at FIDAM, the study coordination centre, for 10 years. Only FIDAM personnel will have access to the data during the study. FIDAM will monitor the flow of participants through each stage of the trial, and finally will be able to publish it.

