### Sample size calculation

A total of 86 patients per group will be necessary to detect a mean difference of 0.3% and a standard deviation of 0.7% in HbA_1c_ reduction between the two treatment groups (Cohen’s *d* = 0.43), with an alpha error = 0.05 and beta = 0.2 (power = 0.8). Given an expected non-evaluable rate of 20%, a total of 216 participants will be needed, with 108 patients in each group.

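### Sample size is for one HbA1c change, but the planned analysis is a three-time-point repeated-measures ANOVA with no primary time point or term named, so 80% power is not assured

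*Protocol article*

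**What the plan says.** **Sample size calculation** (protocol article): "A total of 86 patients per group will be necessary". The purpose of that number is given as "to detect a mean difference of 0.3% and a standard deviation of 0.7% in HbA_1c_ reduction between the two treatment groups". The type I error is set at 0.05 and the power at 80%. Allowance for losses brings the total to 216. No time point is attached to the reduction.

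**Primary outcome**: "The primary outcome will be change in glycaemic control", measured by HbA1c in a central laboratory. Again no time point is given.

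**Assessments**: three points, namely baseline (t0), end of programme (t1) and 6 months after the end (t2). On t1: "The second assessment will occur immediately at the end of the FLASH programme or within 2 weeks after its end". The abstract says that blood is taken at all three.

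**Planned data analysis**: continuous data from the three points are described, differences across time points are calculated within each group, and then "The distributions of these differences will be compared using analysis of variance (ANOVA) for repeated measurements, with the FLASH group as the independent variable". Baseline values become covariates only where the groups differ significantly at baseline. One significance level of 0.05 is given. The section does not single out HbA1c, t1 or t2, and does not say whether a group effect or a group-by-time interaction is tested.

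**The concern.** A sample size supports a power claim only for the test it was computed for. Here that test is a 1-df comparison of one change between two arms. A repeated-measures ANOVA with two follow-ups offers other tests. The group effect on the changes averages t1 and t2, so a smaller effect at t1 dilutes it. The group-by-time interaction over three points spends 2 degrees of freedom. The power of each depends on the size of the t1 effect and on the correlation between the two changes, and the protocol gives neither.

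The t1 effect is a real unknown in this design. By the programme overview (Table 1), therapy adjustment from glucose patterns is taught in week 4 and checked in week 6, and t1 falls at the end of the programme or up to 2 weeks later. The protocol does not say how much of the HbA1c effect it expects by then.

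At stake are whether the main comparison has the power claimed for it, and whether the result that counts as confirmatory is fixed before the data are seen.

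**Working it through.** **1. The plan's own figure.** Inputs from Sample size calculation: difference 0.3, SD 0.7, alpha 0.05 (taken as two-sided), power 0.80.

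n = 2 × (1.960 + 0.842)² × 0.7² / 0.3² = 85.5, so 86 per group. Allowing for 20% non-evaluable, 86 / 0.8 = 107.5, so 108 per group and 216 in total. A one-sided test would need only 68, so the calculation is two-sided. With the t distribution the noncentrality is 0.3 / (0.7 × √(2/86)) = 2.81 on 170 df, and power is 79.8%. The arithmetic is correct, and it belongs to a two-sample test of one change.

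**2. Assumptions needed for the ANOVA.** From the document: 86 per group, effect 0.3 and SD 0.7. The calculation ties neither figure to a time point; I apply the effect to t2 and the SD to each change. Not in the document, so assumed: t1 effect = f × 0.3 with f = 0, 1/3, 1/2 or 1, and correlation r = 0.4 to 0.7 between the t0-to-t1 and t0-to-t2 changes.

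**3. Group effect on the averaged change (1 df).** Effect = 0.3 × (1 + f)/2; SD = 0.7 × √((1 + r)/2). Example with f = 1/2 and r = 0.5: effect 0.225, SD 0.606, noncentrality 0.225 / (0.606 × √(2/86)) = 2.43, power 68%.

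**4. Joint test of both changes (2 df, the multivariate form of the group-by-time interaction).** λ = (86/2) × (0.3²/0.7²) × (1 − 2rf + f²)/(1 − r²), referred to F on 2 and 169 df. Example with f = 1/2 and r = 0.5: λ = 7.90 × 1 = 7.90, power 70%.

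| t1 effect as share of t2 effect | Averaged change | 2-df test |
|---|---|---|
| none | 33–39% | 78–95% |
| one third | 52–61% | 71–81% |
| half | 62–71% | 70–74% |
| full | 86–92% | 78–86% |

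Two features explain the table. The averaged test equals the single t2 test when (1 + f)² = 2(1 + r), that is at f = 0.67 for r = 0.4 and f = 0.84 for r = 0.7; below that it loses power and above it gains. The 2-df test is weakest when f = r. There λ is 7.90, the same as for the t2 contrast alone (2.81²), and the extra degree of freedom brings power down to about 70%.

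**5. Error rate if either time point could count.** For two tests at 0.05, type I error = 1 − P(|Z₁| < 1.96 and |Z₂| < 1.96). This is 9.3% at r = 0.4, 9.1% at r = 0.5 and 8.3% at r = 0.7.

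**The case against.** The strongest reply is that Planned data analysis is a general paragraph for all continuous measures and never calls the ANOVA the primary test. Its mention of all three time points belongs to the descriptive summary. The next sentences can be read as comparing each change between arms. With two time points, the group-by-time test is identical to the two-sample test of change that was sized, and the mismatch disappears. The source is also a condensed article with its figures missing, and an exact model term is commonly left to the analysis plan.

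Much of this stands. It rules out a flat statement that 80% is not the power of the planned test. It does not remove the point: on that reading there are two such changes, t1 and t2, still unranked. The time point of the primary outcome is part of its definition, not a modelling detail. The ANOVA is also the only between-group method given for continuous data, so it covers HbA1c by inference.

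Three stronger readings are tempting and not supported:

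- **The trial is underpowered.** Both ANOVA tests reach or exceed 80% in some cases. If HbA1c has not moved by t1, the 2-df test has 78–95%; if the full effect is there by t1, the averaged test has 86–92%. That HbA1c has little time to respond by t1 is not stated in the protocol.
- **Power is far lower still, because a group main effect over raw values would include baseline.** The text compares differences, and the calculation needs an HbA1c SD that the document does not give.
- **Type I error is roughly doubled.** The protocol nowhere says that any one significant result counts as success, so the inflation is conditional.

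**Conclusion.** The point holds as a mismatch that leaves power undetermined. The sample size is right for one comparison of one HbA1c change, and the analysis section does not commit to that comparison. If a single change is tested, 86 per group gives about 80%. If the three-point ANOVA is followed, power ranges from about 33% to 92% for the averaged change and from 70% to 95% for the 2-df test, depending on a t1 effect and a correlation that are my assumptions. With half the effect at t1, both tests fall short of 80%. If significance at either follow-up were accepted as success, type I error would be about 8.3–9.3% in place of 5%. Confidence is high that no primary time point or term is named in the article; the power figures are illustrations under the assumed ranges.

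**What to change.** State one primary endpoint and one 1-df contrast, for example: the primary endpoint is the between-arm difference in HbA1c change from t0 to t2, tested two-sided at 0.05 with baseline HbA1c as a prespecified covariate; HbA1c at t1 is secondary. The covariate would then no longer depend on a significance test of baseline differences.

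The sample size section names no time point, so t2 is a reasonable choice that the sponsor must confirm. The existing calculation is unadjusted and so slightly conservative for the baseline-adjusted test; 86 evaluable per group and 216 in total can stay.

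If the sponsor prefers the three-point ANOVA, it should name the term tested and restate power with a stated correlation and t1 effect.

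Cost: about two sentences in the protocol and analysis plan, with no added patients, visits or data. The ANOVA alternative also needs a new power calculation and possibly more patients: with the t1 effect at half and a correlation of 0.5, 80% power would take about 106 evaluable per group for the interaction and 115 for the averaged change.
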